### Definition of injuries

For the purpose of this trial, an injury will be defined by the presence of pain that scores at least 30 mm on a 100 mm visual analogue scale when at its worst [21, 22]. Due to the lack of evidence regarding the diagnostic accuracy of the lower limb injuries of interest, the diagnosis of medial tibial stress syndrome [23], patellofemoral pain [36], Achilles tendinopathy [37], and plantar fasciitis/plantar heel pain [21] will be determined using a pragmatic approach via clinical assessments based on definitions described in previous studies (Table 1).

Over the 11 weeks of basic training, participants will document the presence and location of pain on pain drawings in their weekly self-report diaries. The pain drawings will identify the presence and location of pain in the body or feet, but they will not provide a specific diagnosis regarding the cause of pain. Once the self-report diaries have been submitted at the exit interview, the assessors will use a transparent overlay divided into multiple body areas to determine pain location.

### Outcome measures

The *primary outcome measure* will be the combined incidence of the four common lower limb injuries (medial tibial stress syndrome, patellofemoral pain, Achilles tendinopathy, and plantar fasciitis/plantar heel pain) as determined at medical appointments and by assessors at the exit interview (week 11).

*Secondary outcomes* include:(i)the overall incidence of lower limb pain as determined by pain drawings in self-report diaries, measured at week 11;(ii)the severity (usual and worst) of over-use lower limb pain as determined by the 100 mm VAS in self-report diaries, measured at week 11;(iii)the time (in days) to lower limb injury and pain as determined by self-report diaries and navy medical records, measured at weeks 1 to 11;(iv)time to drop-out from injury (in days) as determined by navy administration records, measured at weeks 1 to 11;(v)the type, frequency and severity (mild, moderate or severe) of self-reported adverse events (such as new pains, shoe/insole discomfort and blisters) will be obtained from the self-report diaries, measured at weeks 1 to 11;(vi)lost training days as determined by navy administration and medical records, measured at weeks 1 to 11;(vii)shoe comfort will be measured using a 100 mm visual analogue scale, measured at baseline and week 11;(viii)general health status will be determined using the Short-Form-12 (SF-12) Version 2 questionnaire [31], measured at baseline and week 11.

Shoe comfort will be determined using a 100 mm visual analogue scale, which has been shown to have good reliability [39]. The left end of the scale (0 mm) is labelled “not comfortable at all” and the right end of the scale (100 mm) is labelled “most comfortable imaginable”. Participants will be instructed to place a mark on the scale that represents their perceived comfort rating. Similarly, pain will be determined using a 100 mm visual analogue scale. To indicate the range of pain to participants, the left end of the scale (0 mm) is labelled “no pain” and the right end of the scale (100 mm) is labelled “worst pain imaginable”. The VAS has been shown to be a valid [40] and reliable [39] measure of pain.

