#### Session 2 (week 2)

At this session an assessor will be available to review all participants who are not finding their insoles comfortable. If participants report that the allocated insoles are uncomfortable, the insoles will initially be inspected to ensure that they fit the shoes and foot properly and will be re-moulded as per session 1. If adequate comfort is still not achieved, the section of the insole causing the discomfort will be identified and modified (either by spot heating or by grinding material away in the area of concern). The assessor will attempt to remove the least amount of material required to achieve comfort.

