#### Session 3 (week 11)

An exit interview will be conducted with an assessor that is blinded to group allocation in the final week of training (week 11). This session will be used to collect self-report diaries and confirm their accuracy and completeness with participants. In addition, if lower limb pain is being experienced by the participants at this session, the assessor will attempt to determine the presence of medial tibial stress syndrome [23], patellofemoral pain [36], Achilles tendinopathy [37], and plantar fasciitis/plantar heel pain [21, 38]. Finally, injury data will be cross-checked against ADF medical records.

All participants will remain blinded to their group allocation and will have a similar experience at all sessions regarding time spent with assessors, advice provided, and data collected. That is, the only difference between the groups will be the type of shoe insole received.

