### Adverse events

Adverse events will be documented by participants in weekly self-report diaries. An adverse event will be considered any harmful or unpleasant outcome for which there is a known or plausible association with the shoe insoles and those for which there is none [42].

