## Discussion

This randomised controlled trial is being conducted to determine the effectiveness of prefabricated foot orthoses for the prevention of lower limb overuse injuries. Numerous clinical trials have previously investigated whether foot orthoses prevent injuries; however they are generally of poor methodological quality [9, 14]. Of particular note, the majority of previous trials lacked participant and assessor blinding, and few compared the intervention to a control intervention [9, 14], which is likely to bias or confound the findings [45, 46].

The foot orthosis selected for this trial were chosen for four main reasons. Firstly, prefabricated foot orthoses were considered more practical than customised foot orthoses (made from a cast or mould of the foot) as they can be issued to participants immediately, which is preferable in defence force populations. Secondly, prefabricated foot orthoses are relatively inexpensive compared to customised orthoses. This is an important consideration, as if this study demonstrates that foot orthoses can prevent injuries, cost effectiveness is likely to be a factor when deciding whether foot orthoses become standard issue for defence force recruits. Thirdly, the specific prefabricated foot orthosis (Formthotics®, Foot Science International, Christchurch, New Zealand) was selected as similar devices have been used in large randomised trials with few orthotic-related adverse events being reported [11, 47, 48]. The selected orthosis is made from polyethylene foam and a similar trial reported fewer orthotic-related participant drop-outs in those assigned to an orthosis made from a foam-based material (9 %) compared to a semi-rigid plastic (37 %) [26]. Such factors are important because minimising adverse events and ensuring the orthosis is comfortable is particularly important in this trial as the naval recruits will undertake rigorous activity within days of receiving their allocated shoe insoles. Fourthly, the selected orthosis is commercially available and widely used in clinical practice, which should enable them to be readily utilised as a preventative intervention if they are indeed found to be effective in this trial.

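### Adverse events come from the participant's diary alone, so an event not written there has no stated second route into the safety comparison

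*Protocol article*

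**What the plan says.** Secondary outcome (v), in the Outcome measures section of the protocol article, covers the type, frequency and severity of self-reported adverse events. Its examples are new pains, discomfort from the shoe or insole, and blisters. It says that these "will be obtained from the self-report diaries, measured at weeks 1 to 11". The Adverse events section repeats the source: "Adverse events will be documented by participants in weekly self-report diaries". It also sets a wide definition: "any harmful or unpleasant outcome for which there is a known or plausible association with the shoe insoles and those for which there is none".

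Other outcomes in the same list have further sources. Outcome (iii) is "the time (in days) to lower limb injury and pain as determined by self-report diaries and navy medical records". Lost training days come from navy administration and medical records. The primary outcome uses diagnoses made at medical appointments as well as at the exit interview. Under Session 3, "injury data will be cross-checked against ADF medical records".

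At Session 2, "an assessor will be available to review all participants who are not finding their insoles comfortable". The insole may then be re-moulded, spot-heated or ground. The article does not say that this contact feeds outcome (v).

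Diaries are collected, and checked with the participant, at the week 11 exit interview. Wear time is entered in the diary each week, and a blinded assessor confirms adherence at session 3. The Statistical analysis section excludes adverse events from multiple imputation.

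**The concern.** The definition of an adverse event is broad and its source is narrow. The article assigns sources outcome by outcome, and harms are given only one. Two other places where such events could come to light are already part of the trial: the navy medical records, and the week 2 review, where staff deal directly with insole discomfort, itself a named adverse event. Neither is given as a source for outcome (v).

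The device is preventive, goes to healthy recruits, and could become standard issue according to the Discussion. The Discussion also says that few adverse events and good comfort matter particularly in this trial. If recording is incomplete, event frequencies will be understated. If it is incomplete to different degrees in the two arms, the comparison is distorted as well. The exposed group is those who leave early, because the article describes collection and checking of the diary only at week 11.

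**Working it through.** **Sources named in the article**

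| Item | Diary | Navy records | Staff contact |
|---|---|---|---|
| Primary outcome | not named | medical appointments | week 11 assessor |
| (iii) Time to injury and pain | yes | medical | none named |
| (iv) Drop-out from injury | no | administration | none named |
| (v) Adverse events | yes | none named | none named |
| (vi) Lost training days | no | administration and medical | none named |
| Insole wear (adherence) | yes | no | week 11 confirmation |

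The week 2 review is assigned to no outcome. Shoe comfort, outcome (vii), is measured at baseline and week 11, so it does not record a problem that arises and is corrected in between. Wear is compared between groups by a t-test. A difference in mean wear does not show how many recruits stopped or why.

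**How many recruits might miss the week 11 check**

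Inputs from the Sample size section: 30% incidence, halved to 15%; 80% power; alpha 5% (two-sided assumed); 20% drop-out; total 306.

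The plan's figure first. With the pooled two-proportion formula and mean proportion 0.225:

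n = [1.96 x sqrt(2 x 0.225 x 0.775) + 0.842 x sqrt(0.30 x 0.70 + 0.15 x 0.85)]^2 / 0.15^2 = 120.5, so 121 per arm.

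121 / (1 - 0.20) = 151.25, so 152 per arm and 304 in total, against 306 stated. The figure reproduces closely, and the present point does not depend on it.

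The same drop-out gives 0.20 x 306 = 61.2, about 61 recruits. This is a planning assumption. The article does not say whether the diaries of early leavers are retrieved, so 61 is the size of the exposed group and not a count of lost diaries.

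**What incomplete recording could do**

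The documents give neither adverse event rates nor capture rates, so every input here is assumed: true risk 30% with the orthosis and 20% with the flat insole. Observed risk = true risk x capture.

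| Capture, orthosis / flat | Observed risks | Difference | Ratio |
|---|---|---|---|
| 100% / 100% | 30% v 20% | 10 points | 1.50 |
| 80% / 80% | 24% v 16% | 8 points | 1.50 |
| 60% / 80% | 18% v 16% | 2 points | 1.125 |
| 60% / 100% | 18% v 20% | -2 points | 0.90 |
| 80% / 60% | 24% v 12% | 12 points | 2.00 |
| 100% / 60% | 30% v 12% | 18 points | 2.50 |

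Equal under-capture shrinks the absolute difference and leaves the ratio alone. Unequal capture can hide, reverse or exaggerate a difference, depending on which arm records less.

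**The case against.** The diary is a considered source. Outcome (v) is expressly self-reported, and the diary is meant to hold the very events at issue. It is issued at session 1, so a recruit who attends session 2 with discomfort already has it. Its accuracy and completeness are confirmed at exit. Wear is recorded weekly, confirmed by a blinded assessor and compared between groups. Treated cases of the four target injuries count in the primary outcome, and the cross-check of injury data is not restricted to those four. Participants are blinded and have a similar experience at all sessions. The added sources are not systematic either: the week 2 review is for those with discomfort, and medical entries depend on seeking care. A log of modifications may exist in the study manual.

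Most of this stands, and it rules out three stronger readings that a reader might infer:

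- *Treated, modified or abandoned-insole events are lost.* Not shown. Each can be written in the diary, and stopping wear would show in the wear entries.
- *The loss favours the orthosis.* Not shown. If a contoured insole needs more adjustment, that means more events, not a larger share unrecorded. Unequal capture has to be assumed.
- *The Discussion's 9% for foam devices says how many recruits will stop wearing the insoles here.* It does not. It is orthotic-related drop-out in another trial, a different event from stopping wear while staying in training.

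Nor is the decision not to impute adverse events a fault. Imputing from age and group would not recover a treated blister. It matters only because a missing diary then has no stated back-up.

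The objection does not remove the central fact. The source is fixed in two sections, so this is a stated choice and not a detail left to a fuller document. The exit check is described only for those who reach week 11.

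**Conclusion.** The point holds as a risk of under-ascertainment. An adverse event that the recruit does not enter has no stated second route into outcome (v), although the trial already consults medical records for other outcomes and staff correct insole discomfort at week 2. The risk is greatest for early leavers, about 61 of 306 if the planned 20% drop-out occurs. Neither its size nor its direction can be derived from the documents, and the figures in the capture table are illustrations only.

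This concerns a secondary outcome. The primary analysis and the sample size are unaffected. The change is worth making because it is cheap and the sources are already at hand.

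**What to change.** Name the further sources in outcome (v) and in the Adverse events section, and apply them alike in both arms:

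1. Record each session 2 discomfort complaint and each insole modification (re-moulding, spot heating, grinding), and report both by group.
2. Extend the existing medical-record check to insole-related foot and skin problems, including for recruits who leave before week 11. Keep one record per event across sources, and show the diary-only results beside the combined ones.
3. Derive from the weekly wear entries the proportion who permanently stop wearing the insoles, report it by group, and ask the reason at the exit interview. For those who do not reach that interview, report the reason as not obtained.

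The cost is a short log at session 2, an addition to an existing record check, one derived variable and one interview question, with no new visit. Events must be de-duplicated across sources. Recruitment began on 28 January 2015, so session 2 records may be incomplete for cohorts already past week 2. The report should say which cohorts the log covers.

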### Evaluation of adherence

Adherence to the allocated shoe insoles will be documented by participants each week in self-report diaries. Participants will record the number of hours per day and days per week the shoe insoles have been worn [41]. In addition, adherence to the shoe insoles will be confirmed by a blinded assessor at session 3.

### Adverse events

Adverse events will be documented by participants in weekly self-report diaries. An adverse event will be considered any harmful or unpleasant outcome for which there is a known or plausible association with the shoe insoles and those for which there is none [42].

### Statistical analysis

Statistical analysis will be performed using SPSS version 22.0 or later (SPSS Corp, Chicago, Ill, USA) using the intention-to-treat principle, where all randomised participants will be included in the final analyses. The endpoint will be the completion of the 11 weeks of basic training for each participant. Multiple imputation will be used to replace any missing data using five iterations, with age, and group allocation as predictors [43]. The exception will be for the variable adverse events where no data substitution will be applied.

Participant characteristics and baseline data will be summarised by descriptive statistics. Distribution of continuous variables will be checked for normality and transformation will be carried out if necessary prior to the use of parametric statistics. Outcome data will be analysed according to a pre-planned protocol. Differences in the primary and secondary outcome measures between the two groups will be compared.

The differences between groups for the primary outcome measure of the combined incidence of the four common lower limb injuries (medial tibial stress syndrome, patellofemoral pain, Achilles tendinopathy, and plantar fasciitis/plantar heel pain) and the secondary outcome measure of the incidence of lower limb pain (overall and body region specific) during the 11 week training period will be compared using incidence rate ratios.

In regard to the other secondary outcomes, differences between groups for continuous outcome measures (severity of pain, lost training days and shoe comfort) will be analysed using independent t-tests. The time to lower limb injury and pain and drop-out will be compared using Cox proportional hazards ratios. Adherence of the shoe insole interventions will also be analysed using independent *t*-tests. The difference between groups for the outcome measure of health status (SF-12) will be compared using analysis of covariance (ANCOVA) with baseline scores and intervention group entered as independent variables [44].

95 % confidence intervals will also be provided to indicate precision of point estimates. We will also conduct hypothesis tests where appropriate, which will be considered significant if *p* < 0.05. Effect sizes will be determined using standardised mean differences (Cohen’s *d*) for continuous data.

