## Methods

### Design

The Australian Navy Cerberus Orthotic Research (ANCOR) study is a participant and assessor, parallel-group blinded, randomised controlled trial. Participants will be randomised to a control group (flat insole) or an intervention group (prefabricated foot orthoses). To ensure allocation concealment, permuted block randomisation with random block sizes, stratified by sex, will be undertaken using an interactive voice response telephone service provided by the NHMRC Clinical Trials Centre (University of Sydney, New South Wales, Australia). The end-point for each participant will be the completion of their 11 week basic training programme. The location of the trial will be at the Royal Australian Navy Recruit School, Her Majesty's Australian Ship (HMAS), Cerberus, Victoria, Australia (HMAS Cerberus). The trial has been registered on the Australian New Zealand Clinical Trials Registry (ACTRN12615000024549). The findings from the trial will be reported according to the Consolidated Standards of Reporting Trials (CONSORT) statement [15, 16].

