	Pain is generally worse with prolonged standing or activity; and
	Pain is reproducible with palpation of the medial tuberosity of the calcaneus and/or along the plantar fascia.

Once all baseline measures have been taken, a therapist (separate investigator) located in an adjacent room (with no view of the participants) will allocate participants to one of the two groups (using the allocation system outlined in the manuscript). The therapist will fit and heat the allocated insoles into the participant’s footwear. Once the insoles have been heated, the therapist will place the participant’s footwear on a table outside of their room for the blinded assessor. The assessors, unaware of the insole allocation, will collect the participant’s footwear and advise the participants to wear their footwear for several minutes to allow moulding. Following this, participants will be asked to rate the comfort of their shoes after a brief period of wear (see the ‘outcome measures’ section for more detail). In addition, all participants will be issued with: (i) an information sheet informing them of the recommended wearing-in protocol and how to care for their shoe insoles, and (ii) an individual diary for participants to self-report pain levels over the 11 weeks of basic training. The self-report diaries will consist of body [33] and foot [34] pain drawings, which have been shown to have good to excellent inter- and intra-rater reliability of scoring the location of pain [33, 35]. Each week, participants will be required to indicate the presence and location of pain by shading within the outlines of the pain drawings. If pain is reported, participants will also be required to indicate the usual and worst pain experienced during the previous week on two separate 100 mm visual analogue scales (VAS) (see the ‘outcome measures’ section for more detail). At the completion of the initial assessment, participants will be invited to attend a review consultation the following week (session 2).

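### The imputation model is fixed at age and group allocation, so it omits the baseline SF-12 score that the planned ANCOVA adjusts for, as well as sex, diary pain and departure data that the trial already collects

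*Protocol article*

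**What the plan says.** The protocol article's Statistical analysis section sets one imputation rule for the whole trial: "Multiple imputation will be used to replace any missing data using five iterations, with age, and group allocation as predictors". It then names a single exclusion: "The exception will be for the variable adverse events where no data substitution will be applied". The analysis is "using the intention-to-treat principle, where all randomised participants will be included in the final analyses", so the outcomes of recruits who leave have to be filled in wherever they are not otherwise known. The Sample size section allows for 20% drop-out.

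Other parts of the protocol use or collect variables that this model leaves out:

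- SF-12 is to be "compared using analysis of covariance (ANCOVA) with baseline scores and intervention group entered as independent variables" (Statistical analysis).
- Randomisation is "permuted block randomisation with random block sizes, stratified by sex" (Design).
- In the weekly diary, if there is pain, "participants will also be required to indicate the usual and worst pain experienced during the previous week" (Session 1).
- Secondary outcome (iv) is "time to drop-out from injury (in days) as determined by navy administration records" (Outcome measures).

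**The concern.** An imputation model should contain at least every variable in the analysis model that will use the imputed values. Otherwise the imputed values are drawn as if those relations were zero. The ANCOVA includes baseline SF-12 and the imputation model does not. Imputed week 11 scores therefore dilute the baseline slope and add residual noise, and this happens even when data are missing purely by chance. The imputation is meant to recover information, yet here it gives a less precise comparison than leaving the missing cases out.

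The second matter is plausibility of the missing-at-random assumption. Given only age and group, each leaver whose outcome is missing receives the risk of observed recruits of the same arm and age. The protocol itself expects some recruits to leave because of injury, since it makes that an outcome. If such departures were handled as missing, the imputed incidence of the four injuries would be too low. The article states the predictor list outright, so this is a choice already made, not a detail deferred to a fuller plan.

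**Working it through.** **The plan's own figure.** 30% v 15%, two-sided 5% (sidedness assumed), 80% power, pooled variance, no continuity correction: 121 per group. Then 242/0.8 = 302.5, or 303 to 304 with rounding, against the stated 306. The sample size reproduces and is not in question.

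**SF-12 ANCOVA.** Inputs from the protocol: 153 per group and 20% missing, so 0.8 × 153 = 122.4 observed and 30.6 imputed per group. Assumptions: unit variance within arm, missing completely at random, five imputations (reading the stated five iterations that way), age unrelated to SF-12, and a baseline to week 11 correlation r of 0.4 or 0.6. The protocol gives no value for r.

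1. Baseline slope. Observed cases have slope r and imputed cases have slope 0, so the completed data give 0.8r: 0.60 becomes 0.48, and 0.40 becomes 0.32.
2. Complete-case SE = √[(1 − r²) × 2/122.4]. For r = 0.6: √(0.64 × 2/122.4) = 0.102. For r = 0.4: √(0.84 × 2/122.4) = 0.117.
3. SE under the planned imputation, by Rubin's rules:
   - Within-imputation variance = (1 − 0.64r²) × 2/153, which is 0.01006 at r = 0.6 and 0.01173 at r = 0.4.
   - Between-imputation variance = 2 × 0.2² × (1/122.4 + 1/30.6) = 0.00327. Multiplied by (1 + 1/5), this is 0.00392.
   - SE = √(0.01006 + 0.00392) = 0.118 at r = 0.6, and √(0.01173 + 0.00392) = 0.125 at r = 0.4.
4. Ratio to complete-case: 0.1182/0.1023 = 1.16 and 0.1251/0.1172 = 1.07.

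A simulation of 3,000 trials at each r gave mean SEs of 0.118 v 0.102 and 0.126 v 0.118 (15% and 7% larger), and slopes of 0.48 and 0.32. The mean treatment estimate was about 0.40 SD under every method, which was the true value, so precision is lost without bias. With baseline added to the imputation model, the mean SEs were 0.104 and 0.120.

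**Primary outcome, if injury leavers were set to missing.** True risks are 30% v 15% with 20% leaving each arm. Assumptions not in the protocol: 6% to 10% of controls leave because of one of the four injuries, half that with orthoses, and other leavers have 20% v 10% risk. The imputed risk equals that of completers, (p − cases among leavers)/0.8:

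| Injury leavers | Control | Orthosis | Difference | Ratio |
|---|---|---|---|---|
| 6% v 3% | (0.30 − 0.06 − 0.14 × 0.2)/0.8 = 26.5% | (0.15 − 0.03 − 0.17 × 0.1)/0.8 = 12.9% | 13.6 points | 0.49 |
| 10% v 5% | (0.30 − 0.10 − 0.10 × 0.2)/0.8 = 22.5% | (0.15 − 0.05 − 0.15 × 0.1)/0.8 = 10.6% | 11.9 points | 0.47 |

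**The same inputs, with injury leavers counted as cases.** Only the other leavers are then imputed, at the observed risk in their arm:

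- 6% v 3%: (0.8 × 0.265 + 0.06)/0.86 = 31.6%, and (0.8 × 0.12875 + 0.03)/0.83 = 16.0%. Difference 15.6 points, ratio 0.51.
- 10% v 5%: (0.8 × 0.225 + 0.10)/0.90 = 31.1%, and (0.8 × 0.10625 + 0.05)/0.85 = 15.9%. Difference 15.2 points, ratio 0.51.

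The downward bias disappears. The small upward shift comes from the lower risk assumed for the other leavers.

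**The case against.** The strongest reply concerns the primary outcome. A reader might infer from the first set of figures that the main result will be biased and that power falls to about 71% to 77%. The documents do not support that. Outcome measures takes the primary outcome from medical appointments as well as the exit interview, Session 3 adds a cross-check of injuries against defence medical records, and departures because of injury come from navy records. A recruit who leaves with one of the four injuries would probably have it on record and be an observed case, and nothing in the protocol sets such a recruit to missing. The planned comparison is also a ratio, and that ratio hardly moves even in the unfavourable scenario. This reply stands. It leaves two gaps: the Statistical analysis section does not say how leavers with a recorded injury are classified, and the stability of the ratio depends on departure working alike in both arms.

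A reader might also infer from the words on any missing data that times to injury, pain and drop-out will be imputed. That over-reads the text. Those outcomes are assigned to Cox models, in which a recruit who leaves without an event is censored, not missing.

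On SF-12, it can fairly be said that this is the last of eight secondary outcomes and that a larger SE errs on the cautious side. Both are true and limit the severity, but the mismatch remains. On sex, stratification balances it between arms, so its omission costs mainly precision. Diaries are handed in at the exit interview, so those of leavers may be incomplete and will help only for the weeks available.

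**Conclusion.** The point holds as a specification that should be corrected, not as a fatal flaw. What is certain from the text is that the imputation model omits a covariate of the planned SF-12 ANCOVA. Under 20% missing completely at random this dilutes the baseline slope by 20% and makes the treatment SE about 6-7% (r = 0.4) to 15-16% (r = 0.6) larger than in a complete-case ANCOVA, without biasing the treatment estimate. The correlations are assumptions.

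Understatement of injury incidence is conditional. It needs departure to depend on pain or injury beyond age and group, and the injury to be absent from medical records. In that case incidence is too low in both arms, and the ratio is about 0.47 to 0.49 against a true 0.50 unless departure differs by arm. The document gives only the overall 20% drop-out, so the size of this effect cannot be fixed from it.

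A higher number of imputations and an added sensitivity analysis are matters of preference, and the finding does not rest on them.

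**What to change.** Replace the two-predictor rule with an imputation model that contains group, age, sex, the baseline value of each outcome that has one, every covariate of the corresponding analysis model, diary pain for the weeks available, medical attendance, and the time and reason of departure. State that a leaver with a recorded qualifying injury is counted as an observed case before any imputation. A short clause confirming that times to event are censored at departure would remove the ambiguity about scope.

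The cost is a longer variable list in the same software and a few sentences in the analysis plan. The protocol already has these variables measured or available from its records, so no new data collection is needed.

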### Sample size

A prospective sample size calculation has estimated that 306 participants (i.e. approximately 153 participants per group) are required to provide 80 % power to detect a clinically worthwhile difference of a 50 % reduction in injury in the intervention group (alpha set at 5 %). The sample size for the study was calculated assuming: (i) a combined incidence of injury of 30 % for medial tibial stress syndrome, patellofemoral pain, Achilles tendinopathy, and plantar fasciitis/plantar heel pain, and (ii) a drop-out of 20 %. The estimated incidence of lower limb injury was based on published data from studies investigating injury among Defence members completing basic training [2, 23, 24]. The drop-out rate for this trial was conservatively selected at the higher end of previous trials investigating the use of foot orthoses for the prevention of injuries in defence settings [25, 26], while also taking into account the completion rate of naval recruits undertaking the 11 weeks of basic training at HMAS Cerberus in the previous 12 months.

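### Five imputed data sets leave avoidable Monte Carlo error in the primary test; type I error holds, but a result near p = 0.05 can change verdict with the random seed

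*Protocol article*

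**What the plan says.** Under Statistical analysis, the protocol follows intention to treat, so that "all randomised participants will be included in the final analyses". Gaps are filled by imputation: "Multiple imputation will be used to replace any missing data using five iterations, with age, and group allocation as predictors". Adverse events are the one exception. Groups are compared on the primary outcome by an incidence rate ratio, and hypothesis tests are run where appropriate, "which will be considered significant if *p* < 0.05".

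Under Sample size, the calculation allows for "a drop-out of 20" per cent and explains that "The drop-out rate for this trial was conservatively selected at the higher end of previous trials". Under Outcome measures, the primary outcome comes from medical appointments as well as the week 11 exit interview. Under Session 3, injury data are also checked against Defence medical records.

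**The concern.** Multiple imputation replaces each missing outcome with random draws, so the pooled estimate and its standard error both carry simulation noise that shrinks as the number of imputed sets grows. With five sets and an appreciable share of outcomes missing, the noise is not negligible beside the standard error. Only one run will be reported. If its p-value falls near 0.05, the declared verdict may reflect the seed rather than the data, and an analyst who repeats the same plan with another seed may reach the opposite conclusion. A little power is also lost.

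The word used adds to the difficulty. In imputation software an iteration is usually a cycle of the algorithm, whereas the quantity that governs this noise is the number of completed data sets.

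**Working it through.** **Inputs.** From Sample size: 153 per group, control incidence 30%, a 50% reduction (so 15%), alpha 5%, power 80%, drop-out 20%. From Statistical analysis: five, read as m = 5 imputed sets; predictors age and group; threshold 0.05. Assumed here: two-sided test; outcomes missing completely at random; age uninformative; a log risk ratio over the fixed 11 weeks in place of a rate ratio. The share of missing primary outcomes is not stated, so 5%, 10% and 20% are all shown.

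**The plan's own figure.** With the pooled-variance formula for two proportions (mean 0.225):

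n = [1.960 × √(2 × 0.225 × 0.775) + 0.842 × √(0.30 × 0.70 + 0.15 × 0.85)]² / 0.15² = 120.5, so 121 per group.

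121 / 0.80 = 151.25, so 152 per group and 304 in all. The stated 306 is reproduced to within rounding or a small variation in formula.

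**Size of the noise.** At 20% missing, about 31 of 153 outcomes per group are imputed and 122 observed. The simulated fraction of missing information is about 0.20. The seed-to-seed SD of the pooled estimate, in units of its standard error, is approximately √(0.20 / m):

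- m = 5: √0.04 = 0.20
- m = 50: √0.004 = 0.063

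The standard error also varies between seeds, so the spread of z is somewhat larger: in simulation about 0.25 at m = 5, 0.12 at m = 20 and 0.075 at m = 50.

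**Method of simulation.** Within each group a risk is drawn from its posterior and missing outcomes are drawn from that risk. Results are pooled by Rubin's rules with a t reference, and the same data are re-imputed under many seeds.

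**Single data sets**, 122 observed per group. Each cell gives the central 95% range of p across seeds and the share of seeds with p < 0.05.

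| Events, control v orthosis | m = 5 | m = 50 |
|---|---|---|
| 37 v 18 (expected effect) | 0.001 to 0.038; 99% | 0.003 to 0.009; 100% |
| 37 v 22 | 0.009 to 0.110; 75% | 0.019 to 0.041; 99.9% |
| 37 v 23 | 0.013 to 0.135; 55% | 0.029 to 0.058; 86% |

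**Across all simulated trials at the design effect (30% v 15%).**

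| Primary outcomes missing | Two seeds disagree, m = 5 | Two seeds disagree, m = 50 | Power gained with m = 50 |
|---|---|---|---|
| 20% | about 10% | about 2.5% | about 3 points (76% to 79%) |
| 10% | about 5% | about 1% | about 1 point |
| 5% | about 3% | about 1% | under 1 point |

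If the true rates were 30% v 20%, two seeds would disagree in about 12% of trials at 20% missing with m = 5, and in about 3.5% with m = 50.

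**No true effect.** At m = 5 the type I error is 4.4% to 4.9% across the three levels of missingness.

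**The case against.** The strongest reply is that five imputations remain valid. Rubin's rules with a t reference allow for a small number of sets, and the simulated type I error confirms it. This stands: the cost is noise and a little power, not bias. A reader might infer that five sets make a false positive more likely; the check shows otherwise.

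A reader might also infer that the protocol expects 20% of primary outcomes to be missing. It does not say so. The 20% is an allowance set deliberately high, and a recruit who leaves early may already have a diagnosis on the medical record. The true share may be well below 20%, which is why the range is shown. At 5% missing the effect is small, though not nil.

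A third tempting reading is that the trial's verdict will generally hang on the seed. In simulations at 30% v 17%, among data sets with a typical p between 0.02 and 0.10, 27% to 29% of re-runs with five sets fall on the minority side. That figure is conditional on a result already near the threshold, and 17% is not the design rate. The unconditional figures at 30% v 15% are the fair measure.

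A recorded seed makes any number of sets exactly repeatable on the same software, and fixing it is commonly left to the analysis plan, so its absence here is no fault. But a seed only makes one draw repeatable; it does not make that draw less arbitrary. Finally, if the five does mean cycles of the algorithm, the number of sets is simply not given in this article and the figures above do not apply. The wording would then still need clarifying.

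**Conclusion.** The point holds as a cheap improvement, not as a flaw that invalidates the analysis. On the natural reading, five imputed sets leave avoidable Monte Carlo error in the primary test. At the design effect two seeds disagree in roughly 3% to 10% of trials as missingness rises from 5% to 20%, and 50 sets cut this to roughly 1% to 2.5%. The exposure is confined to results near p = 0.05: at the expected result, 99% of seeds agree even with five sets. More sets reduce the problem at the boundary without removing it, since 37 v 23 still splits 86% to 14% at m = 50. The sizes rest on the assumptions listed with the calculation, chiefly the share of primary outcomes actually missing and the use of a risk ratio.

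**What to change.** In Statistical analysis, replace the phrase about five iterations with a statement that at least 50 imputed data sets will be created, using the term imputed data sets, and that they will be run with a seed set in advance and recorded. If a number of algorithm cycles was intended, give it separately, in the analysis plan if preferred. The change costs minutes of computing and one edited sentence. It touches no participant, visit, sample size or procedure, and can be made before unblinding even though recruitment has begun.
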